## Abstract

**Background:**

Knee osteoarthritis is a common clinical chronic degenerative disease associated with high morbidity and long-term disability. Previous studies have confirmed the efficacy of acupuncture on knee osteoarthritis. Fire needle acupuncture is a combination of heat and acupuncture, which may be more effective than the commonly used filiform needle acupuncture. This study is designed as a randomized controlled trial to evaluate the efficacy and safety of fire needle acupuncture compared to filiform needle acupuncture in knee osteoarthritis patients.

**Methods and analysis:**

This is a prospective randomized controlled superiority clinical trial to evaluate the efficacy and safety of fire needle acupuncture compared to filiform needle acupuncture for knee osteoarthritis. A total of 100 participants will be randomly assigned to two different groups. Participants will receive fire needle acupuncture treatment in the fire needle group, while participants in the filiform needle group will be treated with a filiform needle at the same acupuncture points as the fire needle group. All participants will receive 6 weeks of treatment (2 times per week). The primary outcome is the change of the Western Ontario and McMaster Universities Osteoarthritis Index, and the secondary outcomes include the change of the visual analog scale and 12-item Short Form Health Survey from baseline to endpoint.

**Ethics and dissemination:**

Ethical approval of this study was granted by the Research Ethical Committee of Beijing Hospital of Traditional Chinese Medicine Affiliated to Capital Medical University (2018SB-066). Written informed consent will be obtained from all participants. Outcomes of the trial will be disseminated through peer-reviewed publications.

**Trial registration:**

Chinese Clinical Trial Registry ChiCTR1800019579. Registered on November 18, 2018

## Background

Osteoarthritis [1] is a chronic degenerative disease, which is caused by the imbalance between synthesis and degradation of articular chondrocytes, extracellular matrix, and subchondral bone tissues, under the combined action of biological and mechanical factors. Characterized by joint pain, tenderness, stiffness, joint swelling, limited mobility, and joint deformity, osteoarthritis is a common disease in middle-aged and elderly people, with an overall prevalence of primary osteoarthritis in people over 40 years old of 46.3% and in people over 70 years old of 62.1%. Increasing with age [2], it consumes a large amount of financial and medical resources and has become a serious social burden. A previous study showed that the most commonly affected joint in osteoarthritis is the knee joint [3].

The treatments for osteoarthritis include education, physical therapy, surgical intervention (minimally invasive surgery and conventional surgery), and pharmacological treatment. The pharmacological treatment mainly includes fast-acting medicines, such as non-steroidal anti-inflammatory analgesics, and slow-acting medicine, such as glucosamine sulfate and pentosan sodium polysulfate. In addition, sodium hyaluronate and hormones can be injected into the joint cavity to relieve symptoms. However, the effect of the pharmacological treatments is relatively short, and there are potential adverse events [4, 5]. Adverse events reported include minor gastrointestinal side effects by glucosamine [6–8], renal side effects by non-steroidal anti-inflammatory drugs [9], and cartilage volume loss by intra-articular (IA) corticosteroids [10].

Acupuncture therapy is a simple, inexpensive, and minimally invasive treatment, which has been applied in clinical practice in more than 160 countries and has become the mainstream of complementary and alternative medicine all over the world. Traced back to the Han Dynasty, it was already recorded in *Huangdi Neijing* that acupuncture could treat osteoarthritis, and the efficacy has been confirmed by numerous modern clinical trials and mechanism researches [3, 11, 12]. It is reported in the Cochrane systematic review that acupuncture has clinically relevant short-term improvements in osteoarthritis pain and function, though the benefits are small, and do not meet the pre-defined thresholds for clinical relevance [13]. However, following feedback from Osteoarthritis Research International members on the draft guidelines and six Delphi rounds consensus, acupuncture has been recommended for knee osteoarthritis as a non-pharmacological method [14]. Our team hopes to add clinical evidence by this trial and lay the foundation for subsequent trials.

Fire needle therapy is a special type of acupuncture, which uses specially heated and burned-red needles inserted into the acupoints or affected body region to improve symptoms. Combining heat and acupuncture, it can improve blood circulation with the help of thermal stimulations, promote the reduction of chronic inflammation, and enhance tissue regeneration [15], effectively relieving tissue edema and muscle spasm. Many doctors and therapists in China often use fire needles to treat knee osteoarthritis and find that it is effective.

Among all types of needles, the filiform needle acupuncture is commonly used in acupuncture therapy. There are some randomized controlled trials comparing the efficacy of filiform needle acupuncture and fire needle acupuncture for knee osteoarthritis. However, these studies lack scientific rigor and had a small sample size, non-standardized controls, and unfavorable outcomes.

Therefore, we designed a randomized controlled trial to evaluate the efficacy and safety of fire needle acupuncture compared to filiform needle acupuncture in knee osteoarthritis patients.

## Methods

### Study design

This is a prospective randomized controlled superiority clinical trial to evaluate the efficacy and safety of fire needle acupuncture compared to filiform needle acupuncture for knee osteoarthritis. One hundred participants with knee osteoarthritis will be randomly allocated to the fire needle and filiform groups at a 1:1 ratio. The schedule of enrollment, interventions, and assessments is summarized in Table 1, and the flow diagram of the study procedure is presented in Fig. 1. Patient recruiting is from November 2020. The study protocol has been reported in accordance with the Standard Protocol Items: Recommendations for Clinical Interventional Trials (SPIRIT) guidelines (Additional file 1).

**Table 1. Tab1:**
[figure not shown]
Clinical study schedule

^1^The demographic data includes age, sex, height, weight, ethnicity, marital status, and occupation

^2^The medical history includes the course of the disease, past history, the history of present illness, the history of allergy, concomitant diseases, and medication

^3^The patients’ sitting vital signs will be measured after 10 min of quiet rest

**Fig. 1. Fig1:**
[figure not shown]
Work flow

### Recruitment

Trial participants with knee osteoarthritis will be recruited from outpatient clinics at the Beijing Hospital of Traditional Chinese Medicine, Capital Medical University. Meanwhile, information flyers introducing the details of the trial will be posted at the outpatient clinics for greater exposure.

### Study procedure

This study consists of two phases including (i) a baseline phase (week 0) and (ii) a 6-week treatment phase (week 1 to week 6).

Once potential participants show interest in this trial, they will be invited to attend an eligibility assessment in which their eligibility will be assessed by trial investigators; thereafter, eligible participants will be enrolled and randomly assigned to either the fire needle group or the filiform needle group and given a 6-week treatment.

### Participants

#### Inclusion criteria

Participants who meet all of the following requirements will be considered for inclusion: (1) diagnosed as having osteoarthritis according to *American College of Rheumatology Clinical Classification Criteria for Osteoarthritis of the knee*, (2) graded II–III of Kellgren-Lawrence Radiographic Classification [16], (3) aged between 30 and 75 years old, (4) VAS score of knee joint pain is over 4 out of 10, (5) received no medication or relevant treatment in the past 2 weeks, and (6) provided written informed consent.

#### Exclusion criteria

Patients will be excluded if they have (1) non-primary knee osteoarthritis (e.g., secondary knee osteoarthritis, inflammatory, or other rheumatic diseases); (2) history of trauma, surgery, meniscus or ligament damage, or severe joint deformity on knee joint; (3) serious cardiovascular, cerebrovascular, lung, liver, spleen, kidney or hematopoietic system diseases, tumors, hemorrhagic diseases, or mental diseases; (4) difficulty in cooperating with the examination and receiving quantitative evaluation; (5) female participants who are pregnant or lactating; and (6) cicatricial or hypersensitive to acupuncture treatment.

### Randomization and allocation concealment

The randomization will be performed by the Research Centre of Clinical Epidemiology, Peking University Third Hospital. A block randomization method will be used to generate the random allocation sequence; predetermined computer-generalized randomization opaque sealed envelopes will be used to ensure the allocation concealment. The opaque sealed envelopes, with the participant’s screening order printed outside and randomly assigned group printed inside, will be numbered consecutively and connected into a strain. Researchers will enroll the eligible participants after screening, then separate and open each envelope from the strain in the sequence corresponding to the participant’s screening order and assign the eligible participant into either the fire needle group or filiform needle group.

The statistician who generates the randomly assigned sequence is not the same person as the researcher who decides whether the subject is qualified. People who generate or save the randomly assigned sequence cannot participate in the trial process.

### Blinding

Outcome assessors and personnel involved in data collection and data analysis will be blinded to participants’ group allocation throughout the entire trial. The acupuncturist and participants cannot be blinded due to the nature of the intervention, but they will be informed not to communicate with outcome assessors regarding treatment procedures and responses.

### Intervention

All participants will receive the allocated intervention twice a week for 6 weeks. All participants will go through a standardized interview and be provided with details of the study. The acupuncturist who perform treatments for both groups are registered with the Ministry of Health of the People’s Republic of China as Chinese medicine practitioners and have more than 20 years of clinical experience. Before the trial begins, all acupuncturists will receive special training regarding the purpose and standard procedure of the trial, treatment strategies, and quality control. The treatment details will be fully documented in accordance with the Standards for Reporting Interventions in Controlled Trials of Acupuncture (STRICTA) [17] and Good Clinical Practice guidelines.

#### Fire needle group

Acupoints including the ashi point (local pain point), bilateral ST34 (Liangqiu), bilateral SP10 (Xuehai), bilateral ST35 (Dubi), bilateral EX-LE4 (Neixiyan), and bilateral GB34 (Yanglingquan) will be acupunctured, using a tungsten manganese alloy fine fire needle with a size of 0.5× 25 mm. All locations of the acupoints will be identified according to *The Location of Acupoints*—the national standard of the People’s Republic of China (GB12346-90). Operating method (Fig. 2): participants will be treated in the supine position with the knee bent. First, the acupoints will be identified by nail scratches and then sterilized. Then the needle will be rapidly stabbed into place and pulled out, about 0.5 cm deep, three times at each point, when the tip and the middle parts of the needle body have been burned red by an alcohol lamp. After pulling out the needle, pressure will be briefly applied to the needle hole with a sterilized cotton ball to avoid bleeding, and the patients will be asked to keep these areas clean to avoid infection.

**Fig. 2. Fig2:**
[figure not shown]
Fire needle

#### Filiform needle group

The same acupoints will be selected for acupuncture treatment by the filiform needle (the name of the brand is Andi), with a size of 0.3 × 40 mm. According to the patient’s somatotype, vertically stick the needle in 15–25 mm at the points. Operating method (Fig. 3) is mild reinforcing-attenuating, evenly lifting, inserting, and twisting, then retaining the needle for 20 min.

**Fig. 3. Fig3:**
[figure not shown]
Filiform needle

### Outcome measures

The efficacy of the treated patients will be evaluated before treatment and 6 weeks after intervention. The main efficacy indicator is the WOMAC questionnaire for knee pain, stiffness, and function. The secondary efficacy outcomes are VAS for generalized pain and SF-12 for quality of life. The collected information and data will be maintained confidentially.

#### WOMAC (Western Ontario and McMaster Universities Osteoarthritis Index)

WOMAC is a standardized questionnaire used to evaluate the condition of subjects with osteoarthritis of the knee and hip, which assesses the three dimensions of pain, stiffness, and functional limitation [18] with 24 questions. The score range for each question is 0 to 4. The total score of WOMAC is on a scale of 0 to 96, and higher scores indicate more severe symptoms.

#### VAS (visual analog scale)

The VAS score is used to assess knee joint pain. It ranges from 0 to 10, and a higher score means more severe pain. The efficacy evaluation mainly refers to the Outcome Measures in Rheumatological Clinical Trials formulated by the Osteoarthritis Research Society International (OMERACT-OARSI), i.e., the pain has been highly improved when the score decreases ≥ 50% and the absolute value declines ≥ 2; pain has been improved to some extent when the score decreases ≥ 20% and the absolute value declines ≥ 1, which is the minimum variation for clinical significance.

#### SF-12 (12-item Short Form Health Survey)

The SF-12 scale consists of two parts: physical component subscale and mental component subscale. Converted by a specific formula, the total score is on a scale of 0 to 800, and higher scores represent better health. The conversion formula is presented in Fig. 4. The conversion formula is presented in Fig. 4.

**Fig. 4. Fig4:**

Conversion formula

### Safety assessments

Adverse reactions related to acupuncture include pain, fainting, bleeding, hematoma, infection, nerve injury, aggravation of an underlying disease, severe skin allergy, stuck needle (i.e., the therapist feels sluggish and astringent under the needle and has difficulty twisting, lifting, and inserting the needle, and the patient feels pain during the acupuncture process [19]), a bent needle, and a broken needle. The classification of adverse events refers to adverse drug reactions: level 1—safe, without any adverse reactions; level 2—relatively safe. If there are adverse reactions, the participants can be treated sequentially without any treatment of the complication; level 3—there are safety problems and moderate adverse reactions. The participants can continue to receive treatment after the reactions have been taken care; and level 4—the treatment was terminated due to the adverse reaction. Constitutional or local symptoms, signs, and adverse reactions will be dynamically observed and recorded, which will be used for comprehensive analysis.

For adverse reactions related to the trial, the therapists will give symptomatic treatment such as hemostasis, disinfection, and anti-inflammatory according to the specific situation.

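### The named adverse reactions include no thermal skin injury, so the fire needle's characteristic harm rests on a general recording clause and may be under-counted

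*Protocol article*

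**What the plan says.** The protocol article's Study design section describes a superiority trial to "evaluate the efficacy and safety of fire needle acupuncture compared to filiform needle acupuncture for knee osteoarthritis". Safety is therefore to be compared between arms, not only described.

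The Safety assessments section names the reactions: "Adverse reactions related to acupuncture include pain, fainting, bleeding, hematoma, infection, nerve injury, aggravation of an underlying disease, severe skin allergy, stuck needle", then "a bent needle, and a broken needle". Stuck needle is the only item given an explanation: among other signs, the therapist "has difficulty twisting, lifting, and inserting the needle". On grading, the section says "The classification of adverse events refers to adverse drug reactions" and sets four levels:

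- level 1: no reaction;
- level 2: a reaction that needs no treatment;
- level 3: a reaction that is treated, after which the study treatment can go on;
- level 4: a reaction that ends the study treatment.

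The same paragraph closes with a general clause. General and local symptoms and signs, as well as adverse reactions, will be watched for, written down and used in an overall analysis.

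The two techniques differ. In the Fire needle group section the needle is "rapidly stabbed into place and pulled out, about 0.5 cm deep, three times at each point", and this happens "when the tip and the middle parts of the needle body have been burned red by an alcohol lamp". In the Filiform needle group section the technique is "evenly lifting, inserting, and twisting, then retaining the needle for 20 min". The Blinding section states that neither acupuncturists nor participants can be blinded, and that both are told not to discuss treatment or responses with the blinded assessors.

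**The concern.** Heat is what separates the experimental arm from the comparator. Skin injury from heat is the kind of harm that only the experimental arm can produce, so it is the harm on which a comparison of safety should be most explicit. The stated list does not mention it, yet it explains in detail an event that in practice belongs to the filiform technique.

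Events that are named on a list tend to be looked for, while events left to a general clause depend on someone deciding that they are worth noting. If that happens here, harms specific to one arm could be recorded less completely than needle events that are named, and the safety comparison would lose some of its value. The efficacy comparison is not affected.

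**Working it through.** The article states no figure for this point, so the check is a reading of the text and one count of exposure.

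**Step 1: sort the named items** (Safety assessments section).

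| Type | Items | Count |
|---|---|---|
| General, possible in either arm | pain, fainting, bleeding, hematoma, infection, nerve injury, aggravation of underlying disease, severe skin allergy | 8 |
| Defined by needle manipulation | stuck needle | 1 |
| Needle-mechanical, possible in either arm | bent needle, broken needle | 2 |
| Thermal skin injury | none | 0 |
| Total | | 8 + 1 + 2 + 0 = 11 |

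**Step 2: look for thermal harm elsewhere in the article.** Burning is mentioned only as the way the needle is heated (Background; Fire needle group). Scarring appears only in the Exclusion criteria, as a tendency that bars entry. Neither is named as a safety outcome anywhere.

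**Step 3: set the one manipulation item against the two techniques.** Stuck needle is recognised by difficulty in twisting, lifting and inserting. The filiform technique uses all three and then leaves the needle in for 20 minutes. The fire needle is inserted and withdrawn at once, with no twisting and no retention. The item is therefore a filiform event in practice, although the fire needle is inserted too.

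**Step 4: exposure to the heated needle**, from the Intervention and Fire needle group sections.

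- Points: 5 bilateral points × 2 = 10, plus at least 1 local pain point = at least 11.
- Insertions per session: 11 × 3 = 33.
- Sessions: 2 per week × 6 weeks = 12.
- Per participant at full attendance: 33 × 12 = at least 396.
- Across the 50 participants planned for the arm: 396 × 50 = at least 19,800.

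This is exposure, not harm. The article gives no rate of burns, blisters or scars, so no expected number of events follows from it.

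**Step 5: see what the general clause covers.** A burn or blister at a needle site is a local sign, so the clause reaches it. The clause mentions local signs next to adverse reactions, whereas the four levels are worded in terms of adverse reactions. Whether a local thermal sign is carried into the grade thus depends on someone calling it an adverse reaction. The article does not say who does so. Since acupuncturists and participants are told not to discuss responses with the blinded assessors, it is a fair inference, though not stated, that skin reactions would reach the record mainly through people who know the allocation.

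**The case against.** The strongest reply is that nothing is excluded. The list is introduced as a set of inclusions, not as a closed set, and local symptoms and signs must be recorded in both arms. Most named items fit the fire needle as well: its own procedure guards against bleeding and infection, and both are listed. Only 1 of 11 items is tied to manipulation. An independent committee will examine the case report forms and verify the adverse-event record. The contents of Table 1 and the case report form are not shown, and item-level fields are often left to such documents. All of this stands, and it limits the point to a risk.

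A reader might infer three stronger things, none of which the article supports.

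- **That the list tilts the comparison towards the fire needle or hides a risk.** This would need evidence that named items are asked about and unnamed ones are not. The article does not describe the list as a checklist put to participants.
- **That a burn would be graded level 1.** Level 1 requires no adverse reaction at all. By its wording, a burn fits level 2, 3 or 4 according to what is done about it. The Discussion credits heat with therapeutic effects, so a mild thermal reaction might be regarded as expected, but nowhere does the article say that such reactions are exempt.
- **That some number of participants would go unclassified.** That needs both an event rate and a proportion missed, and the article gives neither.

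The reply does not remove the mismatch itself. The article does set out a list, down to bent and broken needles, and that list fits the experimental ingredient badly. The committee's check is on what has been recorded; it may not reveal a reaction that nobody wrote down.

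**Conclusion.** The point holds as a risk of under-counting. Of 11 named reactions, none is thermal, although each fire-needle participant is scheduled for at least 396 insertions under a red-hot procedure and safety is to be compared between arms. Thermal skin events can be recorded, but only through a general clause, with unblinded acupuncturists and participants. Bias in favour of the fire needle is possible and has not been shown, and its size cannot be derived from the article.

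The exposure count assumes full attendance, all listed points treated at every session, and one local pain point. The risk itself rests on the assumption that unnamed events are noted less reliably than named ones. If the case report form already asks about skin injury in both arms, only the wording of the article needs to change. The matter is a worthwhile and inexpensive improvement to the safety data, not a threat to the primary result.

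**What to change.** - Add burn, blister, scar and lasting pigment change at needle sites to the named reactions.
- Ask about them with the same questions in both arms, at each session and at week 6.
- Record every event first, and enter the judgement on whether treatment caused it as a separate field.
- Report, by arm, the number of participants with any event and the number with any skin event, alongside the four-level grade.

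Because answers about burns could reveal the arm, the week 6 skin questions should come after the WOMAC, VAS and SF-12 have been completed, or be asked by someone other than the blinded assessor.

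The cost is a few items on the case report form and a notification to the ethics committee. The safety profile of the fire needle may look less favourable as a result. No treatment procedure, sample size or efficacy analysis changes.

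### The four-level adverse-event scale grades reactions mainly by what was done about them, so a comparison of levels between arms may not reflect harm

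*Protocol article*

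**What the plan says.** All of the grading is in the Safety assessments section of the protocol article. The scale is presented as borrowed: "The classification of adverse events refers to adverse drug reactions". Level 1 is no reaction. The other levels read:

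- Level 2, relatively safe: a reaction occurs, but "the participants can be treated sequentially without any treatment of the complication".
- Level 3: "there are safety problems and moderate adverse reactions", and then "The participants can continue to receive treatment after the reactions have been taken care".
- Level 4: "the treatment was terminated due to the adverse reaction".

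On management, "the therapists will give symptomatic treatment such as hemostasis, disinfection, and anti-inflammatory according to the specific situation". On recording and use, "Constitutional or local symptoms, signs, and adverse reactions will be dynamically observed and recorded, which will be used for comprehensive analysis". The section also lists the expected reactions, from pain and bleeding to infection, nerve injury and severe skin allergy.

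The Blinding section says that "The acupuncturist and participants cannot be blinded due to the nature of the intervention". It also says that outcome assessors, data collectors and analysts are blinded. Under Data management, an independent committee checks the adverse-event record. The Study design section names safety as an aim beside efficacy.

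**The concern.** Intensity of a reaction and action taken on it are different variables. Here they share one ordinal scale, and action does nearly all the sorting. The level therefore depends partly on decisions made after the reaction.

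The article names the therapists as those who treat reactions. It does not say who decides that treatment ends, but that decision can hardly be made without the therapist or the participant, and both know the arm. A participant may be more, or less, willing to return to a heated needle than to a filiform needle after a reaction of the same intensity.

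At stake is the safety half of the trial's aim. The arms could differ in their levels with no difference in intensity. They could also show similar levels while one arm's reactions are more intense.

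**Working it through.** The article gives no event rate or safety sample size for this point, so there is no stated figure to reproduce. The check is a reading of the definitions, followed by an illustration.

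**Step 1. What separates the levels**

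| Level | Reaction | Reaction treated | Trial treatment continues | Intensity condition |
|---|---|---|---|---|
| 1 | no | – | – | – |
| 2 | yes | no | yes | none |
| 3 | yes | yes | yes | *moderate* |
| 4 | yes | not stated | no | none |

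The two action columns alone separate levels 2 to 4. The single entry in the last column is the only intensity grade in the scale.

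**Step 2. Cases put through the definitions**

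- Slight needle pain, after which treatment is ended because of it: level 4.
- A severe skin allergy or a nerve injury (both on the article's own list), managed, with sessions then resumed: it meets the action criterion of level 3. If *moderate* is only a label, a severe event is called moderate. If *moderate* is a condition, the event fits no level.
- The same severe event with treatment ended: level 4, the same grade as the slight pain.

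The order of the levels is therefore not an order of intensity.

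**Step 3. Who influences the level**

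The treating side and the participants are unblinded; the recording and analysing side is blinded. A blinded data collector records an action that unblinded people have already taken, so accurate recording does not remove the dependence on the arm.

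The intervention descriptions suggest one possible route. Pressing the needle hole to prevent bleeding is part of the described fire needle procedure and is not mentioned for the filiform needle, while hemostasis is listed as treatment of a reaction. The same slight bleeding might count as routine care in one arm and as a treated reaction in the other. This is only a possibility, because the article may simply have left that step out of the filiform description.

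**Step 4. Illustration with assumed rates**

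Input from the article: 50 per arm (Sample size calculation). Assumptions: the proportion *r* with a reaction is the same in both arms, intensity is the same, and only the chance *q* of stopping after a reaction differs.

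Expected level 4 participants per arm = 50 × *r* × *q*.

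- Arm with *q* = 5%, *r* = 20%: 50 × 0.20 × 0.05 = 0.5.
- Other arm with *q* = 30%, *r* = 20%: 50 × 0.20 × 0.30 = 3.

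| *r* | *q* = 5% | *q* = 15% | *q* = 30% | *q* = 50% |
|---|---|---|---|---|
| 10% | 0.25 | 0.75 | 1.5 | 2.5 |
| 20% | 0.5 | 1.5 | 3 | 5 |
| 40% | 1 | 3 | 6 | 10 |

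If *q* is 5% in both arms, the gap is nil in every row. If the arm with more stopping were the filiform arm, the gap would reverse. The table shows that a gap is possible; it does not predict one.

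**The case against.** The strongest reply is that the scale is one descriptor among several. Symptoms, signs and reactions are recorded as such, so an infection or nerve injury stays visible whatever its level. The article names no comparison by level; the Statistical analysis section has only a general rule for count data. Data collectors and analysts are blinded, and an independent committee checks the record. Action taken can already be read from the levels. Even 3 versus 0 of 50 gives a two-sided Fisher p of about 0.24. More stopping because of how the needle feels is arguably a real difference in tolerability.

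Much of this stands, and it rules out three stronger readings that a reader might infer:

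- *That the scale expressly calls severe treated reactions moderate.* It does not. That case arises only if sessions continue, and even then the wording is ambiguous.
- *That the trial is unblinded.* Only the treating side and the participants are.
- *That the safety comparison is distorted, or real harm hidden.* Neither is shown. No analysis by level is specified, and the reactions themselves are recorded.

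The reply does not reach the core. The level definitions are a stated rule, not detail left to a fuller document. Blinded recording and committee checks confirm that a level was correctly assigned; they do not turn it into a measure of intensity. Recording symptoms and signs fixes no intensity grade. A tolerability difference is worth reporting, but as discontinuation, which a reader should be able to tell apart from intensity.

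**Conclusion.** The scale mixes action taken with one intensity word and has no severe grade. A mild reaction can receive the worst level, and a severe one that is managed and continued has no clear level. Because action is influenced by people who know the arm, a comparison by level can be biased.

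This is a risk, not a demonstrated effect. It becomes real only if the levels are compared between arms and if treating or stopping at equal intensity differs by arm. Neither its size nor its direction can be derived from the article, and every rate in the illustration is assumed. The primary outcome and its analysis are untouched. The point is of minor to moderate importance and is worth acting on because the remedy is cheap.

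**What to change.** On the adverse-event form, record as separate fields for each reaction: intensity (mild, moderate, severe), seriousness (yes or no), action taken (none; treated and continued; stopped) and relatedness. By arm, compare the number of participants with any reaction and their worst intensity. Report discontinuations due to reactions as a separate count. The four-level grade can still be derived and shown if the sponsor wants it. No change to clinical management is implied.

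The cost is a few extra form fields and table rows. The article says recruitment began in November 2020, so reactions already recorded may need their intensity graded afterwards from the recorded symptoms and signs. That is less reliable than grading at the time, so the change should be made as early as possible.
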